## Abstract

**Background:**

Incisional hernia is a common complication after liver transplantation with an incidence of 5 to 46%. Concerning non-transplant patients, a recently published meta-analysis describes a reduction of the incidence of incisional hernia of up to 85% due to prophylactic mesh replacement in elective, midline laparotomy. The aim of our study is to show a reduction of the incidence of incisional hernia after liver transplantation with minimal risk for complication.

**Methods/design:**

This is an unblinded, randomized controlled trial comparing time to incisional hernia over a period of 12 months between patients undergoing liver transplantation and standardized abdominal closure with or without prophylactic placement of Phasix™ (Bard – Davol Inc., Warwick, RI, USA) mesh in an onlay position. As we believe that the mesh intervention is superior to the standard procedure in reducing the incidence of hernia, this is a superiority trial.

**Discussion:**

The high risk for developing incisional hernia following liver transplantation might be reduced by prophylactic mesh placement. Immunosuppressed patients are at high risk for developing surgical-site infections. We chose a mesh which has anti-inflammatory properties and is fully resorbed after 18 months.

**Trial registration:**

ClinicalTrials.gov, ID: 03222102. Registered retrospectively on 17 July 2018. Protocol version 1.4, 7 October 2018.

**Electronic supplementary material:**

The online version of this article (10.1186/s13063-019-3477-2) contains supplementary material, which is available to authorized users.

## Background

Incisional hernia is a common complication after liver transplantation with an incidence of 5 to 46% [1–12]. The high incidence rate is due to the very reduced general condition of the patients at the time of operation and is also dependent on the surgical technique, the materials used and the experience of the surgeon [13]. The essential immunosuppressive therapy after transplantation has a negative impact on wound healing and leads to the formation of dysfunctional scar tissue.

Artificial mesh is commonly used in ventral incisional hernia repair as described in the literature, but there is yet no scientific paper on the use of prophylactic mesh placement at the time of transplantation. The main reason, therefore, is that immunosuppressive therapy and artificial mesh implantation seem to be contradictory due an increased risk of complications.

Concerning non-transplant patients, a recently published meta-analysis by Borab et al. describes a reduction of the incidence of incisional hernia of up to 85% due to prophylactic mesh replacement in elective, midline laparotomy [14].

The development of Phasix™ (Bard – Davol Inc., Warwick, RI, USA), an absorbable mesh, has given reason to conduct a study aiming at improving the healing process and stability of the abdominal wall. The mesh consists of suture material, which has proven reliability for many years and is characterized by an extremely long absorption rate of 12 to 18 months.

Phasix™ (Bard – Davol Inc., Warwick, RI, USA) is a fully resorbable monofilament mesh consisting of poly-4-hydroxybutyrate (P4HB) (CE-certified) and is licensed for the treatment of hernias. P4HB is degraded by hydrolysis to the monomer 4-hydroxybutyrate (4-HB) which is a naturally occurring metabolite in humans. P4HB has been in clinical use since 2007 as the suture material Monomax® (Braun). Phasix™ (Bard – Davol Inc., Warwick, RI, USA) is comparable in repair strength to non-resorbable conventional mesh. It resorbs after 12 to 18 months and is gradually replaced by the host’s own tissue [15].

In comparison to other fully resorbable meshes, Phasix™ (Bard – Davol Inc., Warwick, RI, USA) shows higher stability over an even longer period. Particularly with regard to the stability during the first few weeks the material is strong enough to bridge the initial phase of healing. The phase of degradation is constant and restricted [16–20].

Preliminary results of a study conducted on rats at the University of Tennessee Health Science Center, Memphis, TN, USA showed a distinct decrease of methicillin-resistant *Staphylococcus aureus* (MRSA)-infected Phasix™ (Bard – Davol Inc., Warwick, RI, USA) mesh compared to other biological implants, which emphasizes its value for use on immunosuppressed patients even more [21].

## Methods/design

### Aim of the study

The aim of our study is to show a reduction in the incidence of incisional hernia after liver transplantation with minimal risks for complications. We believe that the mesh intervention is superior to the standard procedure in reducing the incidence of hernia; therefore, it is a superiority trial.

### Inclusion and exclusion criteria

Patients undergoing liver transplantation due to end-stage liver diseases at the Department of Surgery, Division of Transplantation Surgery, Medical University of Graz will be included after written informed consent has been obtained.

### Inclusion criteria

Age > 18 yearsFirst liver transplantationWritten informed consent provided

### Exclusion criteria

Combined organ transplantRevision surgery after liver transplantationPrevious liver transplantationPatients with a history of previous median laparotomy or transverse upper laparotomy, with a scar length of more than 15 cmPre-existing abdominal hernia, except umbilicalAny signs of inflammation on the abdominal wall before transplantation

### Endpoint

#### Primary endpoint

The primary endpoint of the study is the comparison of the time to incisional hernia over a period of 12 months between the two groups of patients with and without prophylactic mesh placement. Definition of incisional hernia: any detectable defect in the abdominal wall with intra-abdominal contents protruding beyond the aponeurosis [21].

#### Secondary endpoint

Time to incisional hernia over a period of 24 months between the two intervention groupsRate of complications related to mesh placement, e.g., hematoma, seroma, chronic pain, wound dehiscence, mesh infections, mesh removal

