#### Abdominal-wall closure technique – Intervention group

After closure of the fascia in the above fashion a Phasix™ (Bard – Davol Inc., Warwick, RI, USA) mesh is positioned on the anterior rectus sheath with an overlap of 3 cm along the total length and width. Mesh fixation will be done using PDS 3–0 in simple interrupted sutures each at a 5-cm distance along the margin of the mesh. A subcutaneous drainage will be used. For safety reasons the mesh is only implanted by experienced surgeons who have been instructed exactly on how to use it. Complications are handled according to the standards of our department.

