#### Post-surgical data

Duration of invasive ventilation, complications, pulmonary infection, number of postoperatively required units of blood, days to first postoperative stool.

Postoperative complications: wound infection (according to the “New CDC Guideline for the Prevention of Surgical Site Infection”) [23], hematoma needing surgical revision, total subcutaneous drainage flow, seroma after removal of drainage, revision surgery.

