## Discussion

Due to a high incidence of incisional hernia after liver transplantation, patients would profit to a great extent from hernia prevention. Borab et al. [14] showed the benefits of prophylactic mesh placement in elective midline laparotomy, lowering the risk for the need for a second operation due to reducing the incidence of developing an incisional hernia. From our perspective there is a high variance for the incidence of developing an incisional hernia after liver transplantation. This variance is due to the different types of incisions used for liver transplant surgery. The transverse incision with subcostal extension has a high risk for developing an incisional hernia. J-shaped incisions seem to be associated with a lower risk but are still unsatisfactory. Placing a long-term resorbable mesh in an onlay position might improve the stability of the tissue and reduce the forces on the scar during the healing process until the mechanical strength of the resorbable mesh is resolved after 12 months and the scar tissue is stable. From our point view we hypothesize that this technique will reduce the incidence of developing incisional hernia from an estimated 20% to 5%.

For placement of the mesh the fascia needs to be dissected from the fatty tissue; this surgical step is associated with a minimally elevated risk for developing seroma, while the risk for surgical-site infection is reduced by the precise wound-closure technique and the choice of mesh material. The risk for the included patients is very low. The potential risks are wound-healing disorder, seroma, hematoma and mesh infection; all of which are evenly associated with the standard procedure.

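### The secondary safety endpoint is worded around the mesh and does not name surgical-site infection, so it does not give an even-handed comparison of harm between arms

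*Protocol article*

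**What the plan says.** The Secondary endpoint section of the protocol article has two items. The first is time to hernia over 24 months, stated as a comparison of the two groups. The second is the safety item: a rate of "complications related to mesh placement, e.g., hematoma, seroma, chronic pain, wound dehiscence, mesh infections, mesh removal". No comparison between groups is stated for it.

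Other sections bear on how it can be read:

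- **Aim of the study:** hernia is to be reduced "with minimal risks for complications".
- **Abstract, Discussion:** "Immunosuppressed patients are at high risk for developing surgical-site infections".
- **Abdominal-wall closure technique – Intervention group:** the mesh is an addition to the standard closure ("After closure of the fascia in the above fashion a Phasix™ (Bard – Davol Inc., Warwick, RI, USA) mesh is positioned"). The standard group has none.
- **Post-surgical data:** "Postoperative complications: wound infection (according to the “New CDC Guideline for the Prevention of Surgical Site Infection", followed by hematoma needing revision, seroma after drain removal and revision surgery. Nothing restricts these to one arm.
- **Post-surgical visits:** signs of surgical-site infection, signs of seroma and a VAS score at 1, 3, 6, 12, 18 and 24 months, again for all patients.
- **Discussion:** on dissecting the fascia for the mesh, "this surgical step is associated with a minimally elevated risk for developing seroma". Shortly after, the potential risks are given as "wound-healing disorder, seroma, hematoma and mesh infection; all of which are evenly associated with the standard procedure".

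**The concern.** A randomised safety comparison needs an endpoint that a patient in either arm can reach in the same way. This one is defined by its relation to a device that one arm does not receive, and its only infection item is infection of that device. Two distortions are possible, in opposite directions. A deep wound infection in a mesh patient can be counted as a mesh infection, while the same infection in a control has no named place. Conversely, a true excess of wound infection that does not involve the mesh falls under no named item and could be left out. Minimal complication risk is part of the stated aim, and infection is the hazard the article itself singles out in immunosuppressed patients, so the endpoint should be able to answer that question.

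**Working it through.** The article gives no figure for this endpoint, so there is nothing of the plan's own to reproduce. The sample size (81 per group) belongs to the primary endpoint and is not affected.

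**Step 1: the listed items, by arm.**

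| Item in the endpoint | Possible without a mesh? | Named among the data collected in all patients? |
|---|---|---|
| Hematoma | Yes | Yes, if it needs revision (Post-surgical data) |
| Seroma | Yes | Yes (Post-surgical data; Post-surgical visits) |
| Chronic pain | Yes | VAS (Post-surgical visits) |
| Wound dehiscence | Yes | Not by name |
| Mesh infections | No | – |
| Mesh removal | No | – |
| *Surgical-site infection (not listed)* | Yes | Yes, CDC-based (Post-surgical data); signs at each visit |

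Four of six items are arm-neutral and two are not. The infection item is one of the two.

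**Step 2: the possible readings.**

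- *Literal:* every event must be related to the mesh. No control can qualify, and the result is a one-arm rate.
- *Looser:* the phrase names types of wound complication of interest, in either arm. Controls can contribute four of the six items.

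Neither reading gives a balanced comparison of infection.

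**Step 3: the Discussion.** Mesh infection cannot be evenly shared with a closure that uses no mesh. Seroma is called slightly elevated by the mesh step and then included among the evenly shared risks. If standard closure also causes hematoma, seroma and healing disorders, a label of mesh-related cannot separate the mesh's contribution. A comparison of all such events between arms can.

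**Step 4: illustration of size.** Inputs: about 80 analysed per arm (rounded from 81). All complication rates below are assumptions.

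(a) *Literal reading, if the arms were tested against each other.* For 4/80 versus 0/80, uncorrected chi-squared = 160 × (4 × 80)² / (80 × 80 × 4 × 156) = 4.10, p = 0.043. The expected counts are 2 per arm, where this approximation is poor: Fisher gives p = 0.120 and continuity correction p = 0.129. Fisher needs 6 versus 0 (p = 0.028). If 5% of mesh patients had a qualifying event, the binomial chance of at least 4 is 57%, and of at least 6 it is 21%.

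(b) *Looser reading, equal true risk.* Assume 15% non-infectious complications in both arms, plus deep infection in both arms that is counted only where a mesh is present, with no overlap. Summing two binomials (n = 80 each) gives the chance that mesh looks significantly worse:

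| Deep infection, both arms | Counted rates, mesh v control | Chi-squared | Fisher |
|---|---|---|---|
| 3% | 18% v 15% | 7% | 5% |
| 5% | 20% v 15% | 13% | 9% |
| 10% | 25% v 15% | 36% | 29% |
| 15% | 30% v 15% | 64% | 56% |

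With equal counting (20% v 20%), the chi-squared figure is 2.5% and the Fisher figure 1.6%.

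**The case against.** A reader might infer that control-arm infections are excluded by construction and that the comparison is bound to show harm from the mesh. The article does not support that.

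- The list is introduced as examples, so absence from it excludes nothing, and four of its six items can occur in controls.
- No between-arm comparison is stated for this item. The general tests under Planned statistics follow the description of demographic and clinical parameters and are not assigned to it. A descriptive mesh-arm rate would create no false positive.
- No section describes investigators judging whether an event was mesh-related, so bias from unblinded attribution is conjecture.
- Capture is largely arm-neutral and a data monitoring committee is planned. A real rise in wound infection would be recorded and could be compared.
- The sentence on evenly shared risks is Discussion prose and governs no analysis.
- The article condenses a separate study protocol, which may define the components.
- The illustration assumes that deep infections never coincide with dehiscence, seroma or hematoma, and that every one in the mesh arm is called a mesh infection. Any overlap narrows the gap.

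All of this stands against the strong reading and against treating the percentages as findings. It does not rescue the wording. The examples illustrate a qualifier that still ties the rate to the mesh, and the hazard the article stresses is unnamed. Arm-neutral data collection makes the endpoint easy to repair but does not repair it. A rate from one arm alone would also leave the safety aim without a comparator.

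**Conclusion.** The point holds as a defect in endpoint wording. On a literal reading, controls cannot contribute. On a looser one, two of six items, including the only infection item, are confined to the mesh arm, and surgical-site infection is not named. Either way, the endpoint as published does not give an even-handed comparison of harm.

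This rests on the text alone and needs no assumed rates. The size of any distortion cannot be stated: the false-signal figures depend on assumed rates, on no overlap between components and on the choice of test, and they apply only if the arms are formally compared. The primary endpoint, sample size and main analysis are untouched.

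**What to change.** Restate the safety item under Secondary endpoint as the proportion of patients in each arm with any surgical-site complication, irrespective of attributed cause, compared between arms. Give a fixed list: CDC-defined surgical-site infection, seroma, hematoma, wound dehiscence, wound-related revision surgery and chronic pain.

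Report mesh infection and mesh removal separately and descriptively, with patients who received a mesh as the denominator. A mesh infection also counts once as a surgical-site infection in the comparison.

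Reconcile the Discussion: mesh infection should leave the list of evenly shared risks, and the two statements on seroma should agree.

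The cost is mostly wording. Infection, seroma, hematoma needing revision, revision surgery and VAS are already collected without restriction by arm. Dehiscence is not named in the article's data lists, so the case report form should be checked for it. The small downside is that reported complication rates will be higher in both arms, because events count regardless of cause.

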#### Further parameters

Date of birthChild-Pugh score and MELD score prior to liver transplantationImmunosuppression usedBody Mass Index (BMI), height and weightAnamnesis of nicotineDiabetes mellitusHepatocellular carcinomaSystemic corticosteroid therapy prior to transplantationPrior surgery of abdomenAmerican Society of Anesthesiologists (ASA) classification

#### Trial interventions

This is a randomized controlled trial comparing the incidence of incisional hernia between patients undergoing liver transplantation with or without prophylactic mesh placement. The randomization is done using the “Randomizer for clinical trials” from the Institute for Medical Informatics, Statistics and Documentation, Medical University of Graz, Austria . A 1:1 randomization will be performed and patients will be assigned with a randomization number.

### Patient education and study enrollment

As soon as a patient is listed for liver transplantation and no exclusion criteria apply, the patient will be informed about the study (Figs. 1 and 2, Additional file 1 Standard Protocol Items: Recommendations for Interventional Trials (SPIRIT) Figure). When a patient signs the written informed consent, they are enrolled in the study. Afterwards the initial condition of the patient will be assessed and the case report form (CRF) will be filled in. The status of the abdominal wall and the existence of risk factors for development of hernia after liver transplantation will be evaluated (see “Section 4.3”). The patients will be randomly allocated to either the standard of care or the intervention group. To reach target sample size, all patients who will receive a liver transplantation at our center are in ambulant treatment before our study team makes contact with them and comprehensive participant enrollment can then be performed.

**Fig. 1 Fig1:**
[figure not shown]
Standard Protocol Items: Recommendations for Interventional Trials (SPIRIT) Figure. Flow chart of the PRevention of INCisional hernia after liver transplantation (PRINC) trial. *AE* adverse event, *SAE* serious adverse event, *VAS score*, Visual Analogue Scale score for pain

**Fig. 2 Fig2:**
[figure not shown]
Template of content for the schedule of enrollment, interventions and assessments (Standard Protocol Items: Recommendations for Interventional Trials. (SPIRIT) Figure

### Surgical technique

Surgical access is through a midline laparotomy with right lateral extension. Liver transplantation is done using a standard or piggyback technique.

#### Abdominal-wall closure technique – Standard group

The closure of the J-shaped incision is started by placing two to three sutures of Ethibond 2–0 single stitches at the cranial end of the median part of the laparotomy and the far lateral end of the transverse part at a distance of 5–10 mm [22].

For the median laparotomy a full-thickness closure is performed using a PDS 2–0 double loop with intermittent single stitches using Ethibond 2 for augmentation (3–4 cm distance). The posterior sheath of the transverse incision is then closed by a PDS 2–0 double loop, followed by a third PDS 2–0 double loop closing the anterior sheath of the transverse incision. The transverse incision suturing is augmented by intermittently placing Ethibond 2 single sutures (approximately 5-cm distance).

The wound is closed using vicryl 4–0 single stitches for the subcutis every 1–2 cm. Skin closure is performed using staples.

#### Abdominal-wall closure technique – Intervention group

After closure of the fascia in the above fashion a Phasix™ (Bard – Davol Inc., Warwick, RI, USA) mesh is positioned on the anterior rectus sheath with an overlap of 3 cm along the total length and width. Mesh fixation will be done using PDS 3–0 in simple interrupted sutures each at a 5-cm distance along the margin of the mesh. A subcutaneous drainage will be used. For safety reasons the mesh is only implanted by experienced surgeons who have been instructed exactly on how to use it. Complications are handled according to the standards of our department.

### Postinterventional screening

#### Intraoperative data

Duration of operation.

Number of platelet transfusion, erythrocyte transfusion and plasma transfusion.

Operative complications (injuries to the intestine, bleeding).

#### Post-surgical data

Duration of invasive ventilation, complications, pulmonary infection, number of postoperatively required units of blood, days to first postoperative stool.

Postoperative complications: wound infection (according to the “New CDC Guideline for the Prevention of Surgical Site Infection”) [23], hematoma needing surgical revision, total subcutaneous drainage flow, seroma after removal of drainage, revision surgery.

#### Post-surgical visits

Post-surgical visits will take place 1, 3, 6, 12, 18 and 24 months after liver transplantation and include the following specific examinations:Ultrasound examination: detection of clinically non-detectable herniaSigns of infection of the surgical siteSigns of seromaVisual Analog Scale (VAS) scoreImage documentation

#### Data management and statistical analysis

Almost all patients after liver transplantation will receive their post-transplant follow-up in our center; therefore, patients will come for a routine check-up and at the same time this is the follow-up for the study. The data for patients will be collected until 24 months after liver transplantation or until they drop out (revision surgery, death, withdrawal, loss to follow-up). We will use a data monitoring committee (DMC).

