#### Planned statistics

The primary analysis will be for the intention-to-treat (ITT) population including all patients randomized and having had the liver transplantation performed. A per-protocol analysis with all patients without major protocol violations will also be performed.

Demographic and clinical parameters will be displayed with mean and standard deviation and median, minimum and maximum for continuous variables. Categorical variables will be shown via absolute and relative frequency. Furthermore, differences between the groups are calculated using Student’s *T* test or the Mann Whitney *U* test and the chi-squared test. The primary endpoint, time to incisional hernia over a period of 12 months, will be compared using a log-rank test. Additionally, we will also be plotting Kaplan-Meier survival curves by group looking at time to hernia development.

For sensitivity analysis a Cox regression analysis adjusted for age and MELD score will further be performed. Subgroup analyses for immunosuppression therapy (everolimus)-specific differences are planned. A *p* value < 0.05 will be statistically significant. We perform our analyses with SPSS v25.0 (SPSS Inc., Chicago, IL, USA).

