#### Sample size estimation

We estimate from the current data that about 20% of patients will develop an incisional hernia in the standard group 1 year after surgery. In the intervention group in which we use Phasix™ (Bard – Davol Inc., Warwick, RI, USA) the prevalence of incisional hernia should drop to 5%.

Considering these assumptions and a level of significance of 5% and a power of 80%, we need to include 81 patients per group using a log-rank test. With regard to a drop-out rate of 10%, 178 patients need be included in the study.

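### Ending data collection at revision surgery censors patients at an event that may depend on arm and hernia risk, and it conflicts with the stated intention-to-treat analysis

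*Protocol article*

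**What the plan says.** Under Data management and statistical analysis, the protocol article collects data for 24 months after transplantation "or until they drop out (revision surgery, death, withdrawal, loss to follow-up". Revision surgery thus stands beside death and loss to follow-up as a reason to stop observing a patient.

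Under Planned statistics, the primary analysis is intention-to-treat, "including all patients randomized and having had the liver transplantation performed". It makes no exception for patients who are re-operated. The test is log-rank, with Kaplan-Meier curves.

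Elsewhere the same kind of event is an outcome. The Secondary endpoint section counts mesh-related complications, among them "wound dehiscence, mesh infections, mesh removal". The Post-surgical data section records re-operation itself, and haematomas that require it, as postoperative complications.

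The Exclusion criteria also name revision surgery following the transplant, next to previous liver transplantation. The Inclusion criteria admit first transplants only, and Patient education and study enrollment places the approach to patients at listing and enrolment at consent.

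**The concern.** Closure with or without mesh is the randomised treatment. Revision surgery comes after it, so revision is a post-randomisation event. Some revisions will be for the abdominal wall or the mesh: a haematoma, a dehiscence, an infected mesh, a mesh taken out. Such revisions can depend on arm, and they can be linked to the later risk of hernia.

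The log-rank test and Kaplan-Meier estimate assume that a censored patient has the same future risk as those still under observation in that arm. If revised patients differ in risk, and if revision is more frequent in one arm, the comparison is distorted. An analysis plan cannot repair this afterwards, because hernias and complications after revision would not have been collected. The same loss affects the 24-month hernia endpoint and the later part of the complication count.

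**Working it through.** **1. The passages side by side**

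| Section | Role given to revision surgery |
|---|---|
| Exclusion criteria | Reason not to be in the trial |
| Data management and statistical analysis | Drop-out that ends data collection |
| Post-surgical data | Complication to be recorded |
| Secondary endpoint | Overlaps with mesh removal, mesh infection and dehiscence as outcomes |
| Planned statistics | No role: all randomised and transplanted patients are analysed |

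The second and last rows conflict in substance. Revised patients stay in the analysis set, but their outcome is no longer observed.

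The first row has two readings. Applied before randomisation it adds nothing, because only first transplants are eligible. Applied after randomisation it removes patients whom the intention-to-treat definition keeps.

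**2. The plan's own sample size**

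Inputs from Sample size estimation: "about 20% of patients will develop an incisional hernia in the standard group 1 year after surgery", 5% with mesh, significance level 5% (taken as two-sided), power 80%. Allocation from Trial interventions: "A 1:1 randomization will be performed".

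- Hazard ratio: HR = ln(0.95)/ln(0.80) = 0.230.
- Freedman events: (1.96 + 0.84)² × [(1 + HR)/(1 − HR)]² = 7.849 × 2.550 = 20.02.
- Per arm: 20.02/(0.20 + 0.05) = 80.07, rounded up to 81. This agrees with "we need to include 81 patients per group using a log-rank test".
- Total: 162 × 1.10 = 178.2, stated as 178.

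The stated figures reproduce, and the point does not rest on an error in them.

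**3. How few events there are**

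At 81 per arm, 81 × 0.20 = 16.2 hernias are expected in the standard arm and 81 × 0.05 = 4.05 with mesh, 20.25 in all. One unobserved hernia in the mesh arm is about a quarter of that arm's events (1/4.05 = 25%).

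**4. Illustration of lost events**

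The article gives neither a revision rate nor a hernia risk after revision, so the share of hernias lost is an assumption. Each arm's 12-month rate is reduced by that share, HR is recomputed from the reduced rates, and d = 81 × (sum of the two rates). Power = Φ(√d × (1 − HR)/(1 + HR) − 1.96).

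| Hernias lost, standard / mesh | Observed rates | d | HR | Power |
|---|---|---|---|---|
| 0% / 0% | 20% / 5% | 20.25 | 0.230 | 80% |
| 10% / 10% | 18% / 4.5% | 18.2 | 0.232 | 76% |
| 20% / 20% | 16% / 4% | 16.2 | 0.234 | 71% |
| 30% / 30% | 14% / 3.5% | 14.2 | 0.236 | 64% |
| 0% / 30% | 20% / 3.5% | 19.0 | 0.16 | not meaningful (biased) |
| 30% / 0% | 14% / 5% | 15.4 | 0.34 | 49% |

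The calculation leaves patients with a lost hernia in the denominator, which is an approximation. Holding HR at 0.230 in the 30%/30% row gives 3.765 × 0.626 − 1.96 = 0.398, or 65%, so the approximation matters little.

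The last two rows show that unequal loss moves the hazard ratio in either direction, with 0.3 × 4.05 = 1.2 hernias lost in one case and 0.3 × 16.2 = 4.9 in the other.

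**The case against.** Several stronger readings are tempting, and the article does not support them.

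- **Revised patients are removed from the comparison.** A reader might infer this, but the intention-to-treat definition keeps them. Under the drop-out rule they are censored at revision: their time at risk counts, and so does any hernia found before it. Removal would follow only if the exclusion were enforced after randomisation, which the article does not say. That item may merely rule out a re-operation as the index procedure.
- **Harm from the mesh is hidden.** The revision itself is recorded as a complication, and mesh removal is counted. What is lost is what happens afterwards, in both arms.
- **The bias favours mesh.** The direction cannot be known. The Discussion says the main wound risks are shared evenly with the standard procedure, although it also concedes a slightly raised seroma risk from the added dissection, and mesh removal can occur only in the mesh arm.
- **Revisions come on top of the 10% drop-out.** Since revision is listed as a drop-out reason, the natural reading is that the 10% already includes it. The power table starts from 81 per arm, with that allowance used up. Whatever part of the loss the allowance covers costs less power (89 per arm with no loss gives 84%).

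It is also fair to say that the article does not define revision surgery, which may include re-operations unrelated to the wall, and that it condenses a full protocol (version 3.0, named under Trial status) that is not shown.

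These points narrow the concern but do not remove it. The article states that data collection stops at an undefined event after the randomised closure. A larger sample replaces lost numbers; it does not make the censoring uninformative.

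**Conclusion.** The concern holds in this form: the drop-out rule ends observation at revision surgery, which conflicts with the intention-to-treat statement and makes censoring potentially informative for the primary endpoint. It also cuts off later hernias and complications. The exclusion item is ambiguous and needs clarifying, but the article does not show that randomised patients will be excluded under it.

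The size is unknown because no revision rate is given. As an illustration, losing 10% to 30% of hernias equally in both arms takes power from 80% to about 76% to 64%, counted after the drop-out allowance is used up. Losing 30% in one arm only would shift the planned hazard ratio of 0.23 to 0.16 or 0.34. These shares are assumptions. The existence of the problem follows from the text, and its importance from the small expected count of about 20 hernias.

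**What to change.** 1. Remove revision surgery from the drop-out reasons under Data management and statistical analysis.
2. Delete the revision item from the Exclusion criteria, or state that it applies only before randomisation.
3. Follow every randomised and transplanted patient to 24 months for hernia and complications, whether or not a re-operation occurs.
4. In the primary intention-to-treat analysis, count every hernia that meets the article's existing definition up to 12 months, before or after revision. Leave that definition unchanged: dehiscence is listed separately as a secondary outcome and should not be turned into a primary event.
5. Keep censoring at revision only as a labelled sensitivity analysis, and define revision surgery for that purpose.

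The cost is a short amendment. The article says study follow-up coincides with routine check-ups at the centre for almost all patients, so continued observation needs no additional patients and the planned numbers (81 per group, 178 in total) stand. The change concerns data collection and analysis only. Because recruitment began in January 2018, patients already stopped at revision should be brought back into follow-up where consent allows.
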